## Abstract

**Background:**

Type 2 diabetes, also known non-insulin-dependent diabetes, is the most prevalent type of the disease and involves defects in the secretion and action of insulin. The aim of the proposed study is to evaluate the efficacy of pre-exercise low-level laser therapy (LLLT) on muscle performance of the quadriceps femoris in individuals with type 2 diabetes.

**Methods/Design:**

A double-blind, randomized, controlled clinical trial will be carried out in two treatment phases. In the first phase, quadriceps muscle performance will be evaluated using an isokinetic dynamometer and the levels of creatine kinase and lactate dehydrogenase (biochemical markers of muscle damage) will be determined. The participants will then be allocated to four LLLT groups through a randomization process using opaque envelopes: Group A (4 Joules), Group B (6 Joules), Group C (8 Joules) and Group D (0 Joules; placebo). Following the administration of LLLT, the participants will be submitted to an isokinetic eccentric muscle fatigue protocol involving the quadriceps muscle bilaterally. Muscle performance and biochemical markers of muscle damage will be evaluated again immediately after as well as 24 and 48 hours after the experimental protocol. One week after the last evaluation the second phase will begin, during which Groups A, B and C will receive the LLLT protocol that achieved the best muscle performance in phase 1 for a period of 4 weeks. At the end of this period, muscle performance will be evaluated again. The protocol for this study is registered with the World Health Organization under Universal Trial Number U1111-1146-7109.

**Discussion:**

The purpose of this randomized clinical trial is to evaluate the efficacy of pre-exercise LLLT on the performance of the quadriceps muscle (peak torque, total muscle work, maximum power and fatigue index – normalized by body mass) in individuals with DM-2. The study will support the practice of evidence-based to the use of LLLT in improving muscle performance in Individuals with DM-2. Data will be published after the study is completed.

## Background

Diabetes mellitus (DM) is a heterogeneous group of metabolic disorders characterized by hyperglycemia stemming from defects in the secretion and/or action of insulin. Type 2 DM (DM-2), also known non-insulin-dependent diabetes, accounts for more than 90% of cases and is characterized by insulin resistance and a reduction in insulin-producing β cells in the pancreas as a result of interactions among genetic polymorphisms, obesity, a sedentary lifestyle and the ageing process
[1,2].

Diet, drug therapy and physical exercise are highly recommended for weight loss among individuals with DM-2 to improve blood sugar control and avoid the loss of muscle mass
[3]. Cardiovascular and strength training are recommended to enhance physical fitness, muscle mass and strength in these individuals
[4]. Training programs founded on resistance exercises are considered safe and well tolerated by individuals with DM-2, including elderly individuals
[5]. Indeed, resistance training is more efficacious than moderate weight loss for improvements in glycated hemoglobin, which is a commonly employed reference to determine the degree of blood sugar control in individuals with DM
[5,6].

Muscle quality is reported to be significantly lower in patients with DM-2 than individuals without this disease
[7,8]. Thus, such patients often encounter difficulties when performing exercise programs which increases the risk of diminished physical function and the occurrence of comorbidities and even death
[9-11]. Patients with DM-2 seem to activate a limited number of the motor units responsible for muscle contractions, which may be related to the denervation of muscle fibers and/or the increase in intramuscular fat tissue
[12].

Low-level laser therapy (LLLT) is a recent option for enhancing muscle performance and is founded on the application of light in the range of 1 to 500 mW on a given region of the body for the promotion of tissue regeneration, the modulation of inflammation, pain relief
[13] and improvements in muscle fatigue. LLLT is reported to optimize muscle performance in both animals
[14-17] and humans
[18,19]. LLLT also improves levels of biological markers directly related to the recovery of the musculoskeletal system when applied before
[19], during
[20] or after
[21] the execution of physical exercise. This therapeutic modality seems to improve muscle performance via the energy metabolism in cells by stimulating photochemical events and enhancing mitochondrial function in muscle cells
[22]. The structural changes in the mitochondria (size) promoted by LLLT lead to an improvement in cell respiration and the formation of adenosine triphosphate, which provides energy to the cells
[23]. LLLT may be useful in individuals with DM-2, allowing improvements in muscle fatigue and the potentiation of muscle function, with a consequent improvement in exercise capacity and a reduction in the emergence of comorbidities such as diabetic neuropathy.

The hypothesis of the proposed study is that pre-exercise LLLT is capable of improving eccentric muscle performance in individuals with DM-2. If this improvement is confirmed, the use of LLLT can favor the execution of physical exercise and activities of daily living among such patients and avoid the emergence of comorbidities that are common to this disease. LLLT could be widely used in the clinical setting and become an easy-to-administer treatment strategy of considerable value. Moreover, the scientific community is in need of further clinical trials on LLLT involving human subjects for the definition of application parameters, mechanisms of action and the long-term effect on skeletal muscle performance.

The aim of the proposed study is to evaluate the efficacy of pre-exercise LLLT on the performance of the quadriceps femoris (peak torque, total muscle work, maximum power and fatigue index normalized by body mass) in individuals with DM-2.

## Methods/Design

### Overview of research design

A double-blind, randomized, controlled trial will be carried out. The participants will be allocated to four LLLT groups through a randomization process using opaque envelopes: Group A (4 Joules), Group B (6 Joules), Group C (8 Joules) and Group D (0 Joules; placebo). Evaluations will be performed using multidimensional questionnaire, self-perceived fatigue (visual analog scale for fatigue (VAS-F) and Item 2.2 on the WHOQOL-100), Lower Extremity Functional Scale (LEFS), Diabetes Quality of Life (DQOL) measure, Problem Areas in Diabetes (PAID) scale, WHOQOL-BREF, Patient Specific Functional Scale (PSFS), functional evaluations (isokinetic dynamometer, sit-and-stand test, timed up-and-go test (TUGT), functional reach test (FRT)) and blood collection for the assessment of markers of muscle damage and the capillary glycemia test.

The study will be divided into six evaluations and two treatment phases to which all individuals will be submitted.

#### Evaluation 1

After screening, individuals who meet the eligibility criteria will undergo an initial evaluation involving the multidimensional questionnaire, LEFS, DQOL, PAID, WHOQOL-BREF, PSFS, sit-and-stand test, TUGT and FRT. On a separate day, scheduled based on the availability of the individuals, the blood collection, capillary glycemia test and isokinetic dynamometry (maximum voluntary isometric contraction (MVIC) of the quadriceps muscle) will be performed.

#### Treatment phase 1

Immediately after randomization, treatment will be performed with the administration of the LLLT protocol for the respective groups on the quadriceps muscle bilaterally (alternating legs).

#### Evaluation 2

Immediately following LLLT, the groups will perform the isokinetic eccentric muscle fatigue protocol for the quadriceps muscle bilaterally (alternating legs).

#### Evaluation 3

Immediately after the exercise protocol, blood collection, the capillary glycemia test and isokinetic dynamometry (MVIC of the quadriceps muscle bilaterally (alternating legs)) will be performed.

#### Evaluation 4

Twenty-four hours after the exercise protocol, blood collection, the capillary glycemia test and isokinetic dynamometry (MVIC of the quadriceps muscle bilaterally (alternating legs)) will be performed.

#### Evaluation 5

Forty-eight hours after the exercise protocol, blood collection, the capillary glycemia test and isokinetic dynamometry (MVIC of the quadriceps muscle bilaterally (alternating legs)) will be performed.

#### Treatment phase 2

One week after Evaluation 5, Groups A, B and C will receive the LLLT protocol that achieved the best muscle performance in phase 1 and Group D will receive placebo LLLT three sessions per week for a period of 4 weeks (total of 12 sessions).

#### Evaluation 6

Immediately after the 12th session, evaluations will be performed using the LEFS, DQOL, PAID, WHOQOL-BREF, PSFS, sit-and-stand test, TUGT, FRT and MVIC of the quadriceps muscle bilaterally (alternating legs) (Additional files
1 and
2).

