### Procedures

#### Questionnaires

At the beginning (Evaluation 1) and end (Evaluation 6) of the study, the following questionnaires will be employed:

– A multidimensional questionnaire drafted by the researchers addressing clinical and socio-demographic variables (gender, weight, height, age, marital status, time elapsed since the diagnosis of DM-2, schooling, other diagnosed conditions, medications in use and dose of medications in use).

– LEFS: developed in English to evaluate musculoskeletal disorders of the lower limbs
[24], the LEFS consists of 20 items addressing different activities. Each item has a five-option response scale, which is scored as follows: 0 (extreme difficulty or unable to perform); 1 (quite a bit of difficulty); 2 (moderate difficulty); 3 (a little bit of difficulty); and 4 (no difficulty). The maximum score is 80 points, with lower scores denoting greater difficulty
[25]. The LEFS has been adapted and validated for Portuguese, with Cronbach’s alpha = 0.95
[25].

– DQOL: this questionnaire has 46 multiple-choice items for the evaluation of quality of life among individuals with diabetes and is made up of four subscales: satisfaction, impact, social/occupational worries and worries related specifically to diabetes. The response options are organized on a five-point Likert scale: 1 = very satisfied; 2 = quite satisfied; 3 = moderately satisfied; 4 = somewhat dissatisfied; and 5 = completely dissatisfied. For the impact and worries subscales, the items are scored as follows: 1 = never; 2 = rarely; 3 = sometimes; 4 = often; and 5 = always. Lower scores denote a better quality of life
[26]. The DQOL has been translated and validated for Portuguese and demonstrates adequate reliability and validity for patients with DM-2
[26].

– PAID: questionnaire composed of 20 items on the emotional state of individuals with DM (types 1 and 2). Each item has a five-point Likert response scale: 0 = not a problem; 1 = small problem; 2 = moderate problem; 3 = nearly a serious problem; and 4 = serious problem. The score ranges from 0 to 100 points, with higher scores denoting a greater degree of emotional suffering
[27]. The Portuguese version will be used in the proposed study, which has a Cronbach’s alpha = 0.93 for patients with DM-2
[28].

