**Figure 1 F1:**
[figure not shown]
Realization of isokinetic dynamometry maximum voluntary isometric contraction (MVIC) of the quadriceps muscle.

The volunteers will perform the isokinetic eccentric fatigue protocol for the quadriceps muscle bilaterally (Figure 
2), which will consist of 75 isokinetic eccentric contractions of the knee extensors (5 sets of 15 repetitions with a 30-second rest period between sets) at a velocity of 60°.sec^-1^ in both the eccentric and concentric phases, with a 60° range of motion (between 90° and 30° of knee flexion) for each leg. At each contraction, the dynamometer will automatically (passively) position the knee at 30° and will then flex the knee until reaching 90°. The volunteers will be instructed to resist the knee flexion imposed by the dynamometer with maximum force. The instructions will be given first and the volunteers will receive verbal encouragement throughout the exercise. This protocol has proven to be efficient and reliable for exercise-induced muscle damage
[19].

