#### Data analysis

Peak torque determined by the isokinetic dynamometer will be the primary outcome and CK and LDH activity determined from the blood samples will be the secondary outcomes. The Shapiro-Wilk test will be used to test the data with regard to Gaussian distribution. Data will be expressed as mean and standard deviation values. Two-way repeated-measures analysis of variance with the *post hoc* Bonferroni test will be used for inter-group and intra-group comparisons. The level of significance will be set to 5% (*P* < 0.05) for all comparisons. Statistical analysis will be performed using the SPSS program, version 13.0 (Chicago, IL, USA).

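### With no evaluation between 48 hours after the damaging bout and the end of phase 2, within-group change to Evaluation 6 cannot isolate the 4-week course, and the randomised comparison there estimates the whole sequence

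*Protocol article*

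**What the plan says.** The schedule in Overview of research design is an explicit, closed list: "The study will be divided into six evaluations and two treatment phases to which all individuals will be submitted". Maximum voluntary isometric contraction (MVIC), which gives the primary outcome peak torque, is measured at Evaluation 1 (before the bout), at Evaluations 3, 4 and 5 (immediately, 24 and 48 hours after it) and at Evaluation 6 (after the last phase 2 session).

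In phase 1 the groups differ by dose: "Group A (4 Joules), Group B (6 Joules), Group C (8 Joules) and Group D (0 Joules; placebo". All groups then perform 75 eccentric contractions per leg. Isokinetic dynamometry says of this bout: "This protocol has proven to be efficient and reliable for exercise-induced muscle damage".

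Phase 2 follows: "One week after Evaluation 5, Groups A, B and C will receive the LLLT protocol that achieved the best muscle performance in phase 1", while "Group D will receive placebo LLLT three sessions per week for a period of 4 weeks (total of 12 sessions".

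The Questionnaires section has only two in-person time points: "At the beginning (Evaluation 1) and end (Evaluation 6) of the study, the following questionnaires will be employed". The sit-and-stand, timed up-and-go and functional reach tests are likewise scheduled only at Evaluations 1 and 6. CK and LDH are not scheduled at Evaluation 6, so this point does not touch them.

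Data analysis plans a two-way repeated-measures analysis of variance with Bonferroni post hoc tests, which "will be used for inter-group and intra-group comparisons", at the 5% level. It names no reference time for Evaluation 6.

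**The concern.** A 4-week course is normally judged against the state just before it began, and this design does not record that state. The nearest earlier value, Evaluation 5, is taken when the bout's damage may still be present. The only undamaged value, Evaluation 1, precedes both the bout and a laser session whose dose differs by group.

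Within-group tests are planned, so a significant rise to Evaluation 6 could be reported as a benefit of the course when part or all of it is muscle recovering from the bout. The randomised comparison has a narrower limit: it cannot separate the phase 1 session from the course that followed.

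**Working it through.** **1. Timeline.** Three sessions a week for 4 weeks is 3 × 4 = 12 sessions, which reproduces the plan's figure. From the bout to phase 2 is 48/24 + 7 = 9 days. Session 12 falls about 25 to 28 days after the first session (25 if the last week's sessions fall on days 21, 23 and 25). Evaluation 5 to Evaluation 6 is therefore 7 + 25 = 32 to 7 + 28 = 35 days, with no evaluation between.

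**2. What each comparison contains.**

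| Comparison | Included besides the course |
|---|---|
| Within group, Evaluation 5 to 6 | Spontaneous recovery from the bout |
| Within group, Evaluation 1 to 6 | Phase 1 session, the bout, any adaptation to it |
| Active minus placebo, change from Evaluation 5 | Any phase 1 laser effect on the deficit, with sign reversed |
| Active minus placebo at Evaluation 6, or change from Evaluation 1 | Phase 1 session and any lasting effect of it |

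Evaluation 1 precedes randomisation, so it is a proper baseline for the between-group contrast. Evaluation 5 follows randomisation and may be affected by the phase 1 dose.

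**3. Size of the recovery term.** The documents give no deficit, so these inputs are assumptions: placebo MVIC deficit at Evaluation 5 of r = 10, 20 or 30% of Evaluation 1; phase 1 laser reduces it by a fraction p = 0, 0.25 or 0.5; full recovery by Evaluation 6; no effect of the course.

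- Placebo change, Evaluation 5 to 6: r, that is +10 to +30 points.
- Active change, Evaluation 5 to 6: r(1 − p). For r = 10 and p = 0.25 this is +7.5; for r = 30 and p = 0.5 it is +15.
- Active minus placebo: r(1 − p) − r = −rp. For p = 0 this is 0. For p = 0.25 and r = 10 it is −2.5; for p = 0.5 and r = 30 it is −15.
- From Evaluation 1, both changes are 0 under these assumptions.

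Every arm appears to improve from Evaluation 5 although the course does nothing. If phase 1 laser helped, the between-group change from Evaluation 5 favours placebo.

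**4. Carry-over into the randomised comparison.** Assume a 10-point active-versus-placebo difference at Evaluation 5 that decays exponentially with half-life h. The remainder after t days is 10 × 2^(−t/h).

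| h (days) | Start of phase 2, t = 7 | Evaluation 6, t = 35 |
|---|---|---|
| 3 | 2.0 | 0.003 |
| 7 | 5.0 | 0.3 |
| 14 | 7.1 | 1.8 |

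With t = 32, the last two entries at Evaluation 6 become about 0.4 and 2.1. Carry-over is small unless recovery is slow.

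**5. Share of the phase 1 session.** The Low-level laser therapy protocol section gives 120, 180 or 240 J per session over the muscle. With phase 1 energy d and phase 2 energy b per session, the share is d/(d + 12b). The smallest is 120/(120 + 2,880) = 4.0%, the largest 240/(240 + 1,440) = 14.3%, and it is 1/13 = 7.7% if the dose is unchanged.

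**The case against.** The strongest reply is that the trial is randomised and the control is concurrent. Group D does the same bout, has the same recovery time and stays on placebo in both phases, so the bout and ordinary recovery cancel in the contrast at Evaluation 6. That stands. A reader might infer that the phase 2 comparison is invalid, or that recovery would create a false advantage for laser over placebo. The documents support neither. The bias in a between-group change from Evaluation 5 runs against laser if phase 1 works, and carry-over to Evaluation 6 is small on the assumed figures.

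A reader might also infer that the trialists intend Evaluation 5 as the phase 2 baseline, or claim an effect of the course alone. No section says so. The stated aim is the efficacy of pre-exercise laser in general, and the only pairing the text suggests, for the questionnaires, is Evaluation 1 with Evaluation 6. Misattribution is a risk the text leaves open, not a stated intention.

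It can be added that the choice of contrast is commonly left to an analysis plan, which is not shown. That is fair as to the contrast. But the evaluation list is fixed, and no analysis plan can supply a measurement the schedule does not take. Within-group comparisons are planned without any limit on how Evaluation 6 enters them, and that part of the point remains.

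**Conclusion.** The point holds for the within-group comparisons. Neither available reference isolates the 4-week course, and a rise from Evaluation 5 would include recovery in every arm, placebo included. The 10 to 30 points is an illustration resting on an assumed deficit and full recovery by Evaluation 6; the documents give no figure.

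The randomised active-versus-placebo comparison at Evaluation 6 remains valid for the whole sequence of phase 1 session plus course. What it cannot do is attribute the result to the course alone. Since the phase 1 session is about 4 to 14% of the energy an active group receives, this is a matter of attribution and choice of reference. It does not invalidate the trial.

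**What to change.** In Data analysis, state four things:

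- The Evaluation 6 conclusion for peak torque rests on the inter-group difference at Evaluation 6, adjusted for the Evaluation 1 value (for example by analysis of covariance). The questionnaires and functional tests are handled in the same way.
- That difference is the effect of the whole sequence, phase 1 session plus 4-week course, against placebo.
- Evaluation 5 is not used as the reference for Evaluation 6.
- Within-group change to Evaluation 6 is descriptive only.

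This changes no visit, measurement or treatment, and the phase 1 comparisons up to Evaluation 5 stay as planned. The cost is small: within-group significance tests can no longer be cited as evidence for the course.

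Optionally, an MVIC before the first phase 2 session could document how far recovery has gone. It is an added assessment, needing the stretching, warm-up and positioning set out in Isokinetic dynamometry and the blinded assessor at a treatment visit. It would not cover the questionnaires or functional tests. As a post-randomisation value that the phase 1 dose may have affected, it would not by itself isolate a phase 2 effect.

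### In phase 2, Groups A, B and C share one LLLT protocol, but the stated analysis still treats them as separate groups and has no direct LLLT-versus-placebo test at Evaluation 6

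*Protocol article*

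**What the plan says.** All references are to the protocol article.

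- **Allocation** (Overview of research design): "The participants will be allocated to four LLLT groups through a randomization process using opaque envelopes". The groups are A (4 J), B (6 J), C (8 J) and D (0 J, placebo). No other grouping is defined anywhere.
- **Phase 2** (Treatment phase 2): "Groups A, B and C will receive the LLLT protocol that achieved the best muscle performance in phase 1". Group D receives placebo LLLT. The course is 12 sessions over 4 weeks.
- **Evaluation 6**: it follows the 12th session and includes the MVIC of the quadriceps, from which peak torque is taken. No MVIC is scheduled between Evaluation 5 and Evaluation 6.
- **Outcome** (Data analysis): "Peak torque determined by the isokinetic dynamometer will be the primary outcome". No phase or time point is attached to it.
- **Analysis** (Data analysis): "Two-way repeated-measures analysis of variance with the" post hoc "Bonferroni test will be used for inter-group and intra-group comparisons", at 5% for all comparisons. Nothing separates the two phases, and no pooling of A, B and C is mentioned.

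**The concern.** The treatment structure changes between the phases and the analysis does not follow it. In phase 1 there are four treatments and four groups. In phase 2 there are two treatments: the selected LLLT protocol (A, B and C) and placebo (D).

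If the four groups are carried through to Evaluation 6, three things follow.

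- Three of the six inter-group pairs (A-B, A-C, B-C) compare participants who had the same 4-week treatment. The groups still carry their 4, 6 and 8 J labels, so a difference could be read as a dose effect of the 4-week course. It can be only chance or a remnant of the single phase 1 session about five weeks before.
- The question phase 2 is built to answer, 4 weeks of LLLT against placebo, gets no direct test. The group test spreads over 3 degrees of freedom, and each active-placebo pair uses one third of the treated participants (with equal active groups).
- If one model spans all the visits, the group factor means dose up to Evaluation 5, and phase 1 history plus LLLT-or-placebo at Evaluation 6.

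**Working it through.** The article gives no sample size, power, effect size or allocation ratio, so there is no figure of its own to reproduce.

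**Inputs from the article:** four randomised groups; A, B and C on one protocol in phase 2; Bonferroni post hoc comparisons; 5% level.

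**Assumptions:** two-sided tests; equal arms of n (range below); common SD; A, B and C have the same mean at Evaluation 6, which lies d SDs from D; comparisons at one time point only.

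**1. Information.** In units of SD squared:
- one pair (A versus D): variance 1/n + 1/n = 2/n
- pooled (A+B+C versus D): variance 1/(3n) + 1/n = 4/(3n)

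The ratio (4/3)/2 = 0.667, so a pair keeps two thirds and loses one third. If D were twice the size of one active group, the pair would keep (1/2 + 1/3)/(1/2 + 1) = 0.556. At three times the size it would keep (1/3 + 1/3)/(1/3 + 1) = 0.50.

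**2. Required sample for one given pair relative to the pooled contrast (equal arms).** The ratio is 1.5 × [(z(1 − 0.025/m) + z(power)) / (1.960 + z(power))]², where m is the number of pairs corrected for.

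| m | critical z | 80% power | 90% power |
|---|---|---|---|
| 1 | 1.960 | 1.50 | 1.50 |
| 3 (active-placebo pairs only) | 2.394 | 2.00 | 1.93 |
| 6 (all pairs) | 2.638 | 2.31 | 2.19 |

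For m = 6 at 80% power: 1.5 × [(2.638 + 0.842)/(1.960 + 0.842)]² = 2.31.

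**3. Participants per group for 80% power.**

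| d | pooled | 3-df F | pair, m = 1 | pair, m = 3 | pair, m = 6 |
|---|---|---|---|---|---|
| 0.5 | 42 | 60 | 63 | 84 | 97 |
| 0.8 | 17 | 24 | 25 | 33 | 38 |
| 1.0 | 11 | 16 | 16 | 21 | 25 |

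**4. Power in one illustrative case: n = 15 per arm, d = 0.8 (both assumed).**
- Pooled contrast: non-centrality 0.8/√(4/45) = 2.68; power 75%.
- 3-df between-group F, 3 and 56 df: non-centrality 15 × 0.64 × 0.75 = 7.2; power 57%.
- At least one of the three active-placebo pairs significant (simulation): 53% with m = 6, 64% with m = 3.
- One given pair, m = 6: non-centrality 0.8/√(2/15) = 2.19; power 30%.

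In the same simulation with m = 6, 42% of trials showed some but not all of A, B and C significantly different from placebo, although the three were truly identical. A false impression that the groups respond differently is therefore a common result under this assumption.

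**The case against.** The strongest reply is that much of the criticised analysis is inferred. The Data analysis section does not give the number of group levels at Evaluation 6, does not say that all six pairs are tested, and does not say that one model covers every visit. A journal article may leave the contrasts for each phase to an analysis plan that is not shown. This stands as a caution, and the six-pair figures are conditional on it. It does not remove the point: the article does state an analysis, A to D are the only groups it defines, and that analysis does not fit the phase 2 treatments it describes.

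The remaining objections limit how far the point can be taken.

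- A reader might infer that more than half the information is wasted. With equal arms the loss is one third. It passes half only when expressed as required sample for one named pair after correction over all six pairs (1 − 1/2.31 = 57%). The article fixes neither the allocation ratio nor the number of pairs.
- A reader might set 75% against 30% as the cost in power. The 30% is for one named pair after six-fold correction. The F test (57%) and at least one active-placebo pair (53-64%) are fairer comparators.
- A reader might say that the A-B-C contrasts no longer exist. They do: the groups still differ in their randomised phase 1 session. They are simply not contrasts of phase 2 dose.
- A reader might infer that the comparison with placebo is invalid. Comparing randomised arms with Bonferroni correction is sound, and neither bias nor type I error inflation is shown.
- Evaluation 6 is not shown to be the primary time point. Blood collection is not listed there, so among the ranked outcomes only peak torque is affected, not CK or LDH.

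**Conclusion.** The point holds as one of efficiency and interpretation, at should-fix level. Phase 2 compares one LLLT protocol with placebo, and the stated analysis, naturally read, neither tests that comparison directly nor guards against reading A-B-C differences as effects of phase 2 dose.

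A pooled contrast would use the data better under every comparator examined: a one-third loss of information for a single uncorrected pair, and a required sample of 1.5 to 2.3 times for a given pair at 80% power, depending on the correction. The illustrative gain in power is from 53-64% to 75% against the fairer comparators. These figures rest on equal arms and equal means in A, B and C; the power figures also rest on the assumed 15 per arm and 0.8 SD. The mismatch between treatments and groups rests on none of them.

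**What to change.** Divide the analysis by phase.

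- **Phase 1 (Evaluations 1 and 3 to 5):** compare the four randomised groups, as now.
- **Phase 2 (Evaluation 6):** pre-specify one contrast of peak torque, A+B+C against D, at the 5% level, adjusted for Evaluation 1 MVIC. Show A, B and C separately as description only, and state that differences among them are not phase 2 dose effects.
- **Interpretation:** state that the contrast estimates the whole sequence (one phase 1 session plus the 4-week course) against placebo, because no MVIC opens phase 2. It averages over three phase 1 histories.

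If pooling is already intended, one sentence saying so settles the main point. The baseline adjustment is a recommended refinement; the stated error does not depend on it.

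The change affects analysis wording only: no new visits, measurements or participants. The price is that separate claims for A, B and C at Evaluation 6 are given up. Recruitment is under way, so the text should be settled before the statistician is unblinded.
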